**Trial Registration:**

ClinicalTrials.gov NCT03378739; https://clinicaltrials.gov/ct2/show/NCT03378739 (Archived by WebCite at http://www.webcitation.org/701vstDGd)

## Introduction

### Background and Significance

Cardiogenic shock (CS) is the strongest predictor of mortality in patients who experience an acute myocardial infarction (AMI) or who suffer an episode of acute decompensated heart failure (ADHF). Observational studies have indicated that patient populations particularly at risk of developing cardiogenic shock post AMI or post an episode of ADHF include the elderly and patients with concurrent cardiovascular comorbidities [1]. Advances in efforts to provide early identification of CS, revascularization, and restored perfusion have positively affected mortality rates associated with myocardial infarction (MI) and have caused a dramatic fall in deaths associated with AMI in recent decades, while in the patients who develop CS post MI, mortality continues to be persistent and remains as high as 50% [2].

CS, also known as “pump failure” is precipitated by a profound reduction in cardiac output which results in tissue hypoperfusion secondary to a deficit of circulating blood, this lack of perfusion results in increasingly poor clinical outcomes [2,3,4]. Also defined as complete circulatory collapse, CS is characterized by shock occurring after a primary cardiac pathology in which cardiac output has been compromised. It involves refractory hypotension and tissue hypoperfusion secondary to heart failure after correction of preload and the culprit precipitating arrhythmia [2]. CS is representative of a diverse and complex clinical presentation which is the challenge of identification and management of this calamity. The onset of CS can be acute or progressive, as the ischemia representative of CS may develop from an acute, large, primary MI or can occur as a delayed extension of an original MI [2]. CS can occur acutely in patients with no prior history of cardiac disease, or progressively in patients with chronic heart failure [4]. The most common etiology of acute CS is the incidence of an acute coronary syndrome (ACS), specifically ST-segment elevation myocardial infarction (STEMI) or non-ST-segment elevation myocardial infarction (NSTEMI) which collectively has been reported to account for nearly 80% of cardiogenic shock cases [4]. Patients that develop CS post NSTEMI tend to develop dormant CS and are older with more complex cardiac comorbidities [2]. CS is the strongest predictor of mortality post MI. This is thought to result from both ischemic and mechanical complications. Mechanical complications of MI that contribute to CS include: acute mitral regurgitation secondary to rupture of the papillary muscle, rupture of the ventricular septal wall, or tearing of the ventricular wall [4]. CS can also arise from non-ACS causes such as cardiac abnormality (primary, valvular, electrical, or pericardial), decompensated valvular disease, acute myocarditis, hypertrophic cardiomyopathy with aortic obstruction, cardiac tamponade, arrhythmia, traumatic injury to the chest (myocardium), post cardiotomy secondary to coronary artery bypass graft surgery, and progression of congenital lesions [4].

A designated, multidisciplinary shock team is critical in the assessment, implementation, and management of the CS patient. The collaborative efforts of a team which includes a cardiologist specializing in heart failure, a cardiothoracic surgeon, cardiac inteventionalist, and an intensive care unit (ICU) intensivist working to manage the time-dependent clinical scenario will maximize outcomes related to CS [5]. The Cardiogenic Shock team at the Inova Heart and Vascular Institute (IHVI) is comprised of four clinical disciplines: Interventional Cardiology, Acute Heart Failure, Cardiac Surgery, and Critical Care. Their respective roles in the diagnosis, treatment and management of cardiogenic shock are highly specific yet profoundly collaborative. Interventional cardiology is at the vanguard of treatment and is usually the first point of contact. This group assists with mechanical circulatory assist device insertion and management both on hospital admission and throughout hospitalization. They also manage device weaning and escalation of support. The acute heart failure physician specialist helps to determine a patient’s candidacy for temporary and durable mechanical support. The role of the cardiac surgeon is to assist with and evaluate a patient’s candidacy for surgical support services. Finally, the critical care physician is the team quarterback and the central player in identifying the appropriate parties for emergency consultation as well as the advancement and management of the cardiogenic shock patient’s day-to-day care during hospitalization. IHVI CS team goals can be identified as follows: rapid identification of CS as well as its etiology, maximization of survival through the utilization of mechanical circulatory support (intraortic balloon pump; Impella, percutaneous microaxial flow pump; Tandem Heart, percutaneous left ventricular assist device; peripheral extracorporeal membrane oxygenation [ECMO]; central ECMO; temporary vascular assist device; permanent vascular assist device; or transplant) as well as supportive therapies, and the development and implementation of a hemodynamic support plan with mechanical devices in the event of refractory CS [5]. Team-based interventions are crucial in critical illness as in the case of a “code team” (mandated by the Joint Commission on Accreditation of Healthcare Organizations) for the in-house management of cardiac arrest and a rapid response team for decompensating medical surgical patients. CS is similar to these clinical clusters of symptoms and requires the early identification and specific expertise of many disciplines in order to manage this complex condition. The high mortality rate of CS patients can be tempered through early revascularization and the activation and utilization of a multidisciplinary shock team. The time sensitive nature of CS or the dictum “time to support” [6], with both percutaneous and surgical interventions, requires the activation of a multidisciplinary Shock team in order to manage circulatory collapse and the ensuing end organ dysfunction [6] or failure through prompt response and management of any changes in the patient’s condition in addition to early diagnosis.

A review of relevant literature identifies the benefit and recommends the implementation of a multidisciplinary shock team to improve outcomes in patients in danger of imminent circulatory collapse. Proposed recommendations are wide in scope yet highly specialized with respect to the requirements of this patient population. CS associated with acute MI or acute decompensated heart failure should be closely monitored for progression to decompensation and end organ failure. CS should be suspected and investigated post cardiac arrest due to the significant association between the two conditions by a multidisciplinary shock team [7]. Recommended personnel include a multidisciplinary oversight panel as well as experienced medical teams at a given site [7]. Medical, interventional cardiology, anesthesia, thoracic and vascular surgery, intensive care, and radiology [7] must be available to manage CS in a timely manner. The two strongest priorities in CS are hemodynamic stabilization and the rapid reversal of the low output state to maintain end organ perfusion and rapid coronary reperfusion, although not necessarily in that order, are optimally managed by a CS team [8,9]. Rehospitalization and death are most prevalent in the early discharge period [10]. These readmissions are frequently associated with volume overload as opposed to late readmissions which are associated with the natural trajectory of the syndrome for example cardiac remodeling [10]. This identifies the early discharge period as one where the patient is particularly vulnerable and the careful coordination of the multidisciplinary team as well as the transitional team are implemented to ensure that the care is patient-centered, as well as proactive in protection against recurrence of CS [10]. Activation of a coordinated cardiogenic shock team and early outcome specific therapy in a timely and synchronized manner ensures proper allocation of resources and is associated with increased survival in cardiogenic shock [11]^.^ Successful device selection to support heart rate (HR) in underlying CS etiologies is enhanced by a multidisciplinary team approach including; heart failure specialists, interventional cardiologists, and cardiothoracic surgeons, with patients’ preferences accommodated in a timely manner [12].

The implementation and utilization of a designated CS at the IHVI is an effective strategy to mitigate the consequences of cardiogenic shock. The IHVI CS team, founded in 2017, is mobilized for and directed to five goals: (1) the rapid identification of shock through early activation of the CS team and rapid collaborative decision making, (2) early right heart catheterization to facilitate invasive hemodynamic therapy tailored to the patients’ unique presentation, (3) the accelerated initiation of mechanical circulatory support, (4) minimization of vasopressor and inotropic support, and (5) meaningful recovery and survival of the patient [13]. Bi-weekly action and outcomes review are employed to track efficient methodology with the intention of eradicating significant preventable morbidity and death from CS [13]. Utilizing the best and most recent evidence and best practices, a comprehensive care pathway was developed. A six-month training process was focused on individual and team management of the aforementioned five goals, training and rehearsals were implemented to ensure the seamless execution of the adopted algorithms [13]. Prior to implementation of the Cardiogenic Shock team at the IHVI, 30-day survival was approximately 47%, assuming an alpha level of 0.5, two sided. We expect the implementation of an IHVI Shock algorithm to increase 30-day survival by 15%. Thus, 200 subjects in each group provide at least 80% power to detect a statistically significant increase in 30-day survival from 47%.

We propose to study the outcomes associated with CS patients who have been managed by the CS team at the IHVI in order to ascertain the effects on outcome and survival rate. Positive effects in outcomes and survival will indicate a positive correlation between meaningful survival and management by a multidisciplinary shock team. The database compiled from these outcomes will also serve as a clinical archive of distinctive patient characteristics and outcomes to support future evaluation and translational research. The benefit of CS management to patients is a decrease in disability and mortality post CS episode.

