#### Number of Subjects

Our goal is to include approximately 200 patients before and 200 patients after initiation of Shock team. The study group will consist of a retrospective review of all patients receiving Shock Team intervention after diagnosis with acute decompensated heart failure cardiogenic shock, or acute myocardial infarction cardiogenic shock, from January 1, 2017 until Institutional Review Board (IRB) filing of protocol. A second group will consist of current patients receiving shock team intervention.

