### Statistical Considerations and Data Analysis

#### Sample Size

We are estimating 300-400 patients will be included in this analysis. This size is based on prior smaller studies.

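### The power statement prints a two-sided alpha of 0.5 and an increase of 15% with no scale, and the lower end of the separate 300-400 size estimate misses the stated 80% power

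*Protocol article*

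**What the plan says.** The end of Background and Significance holds the only power calculation. It gives the baseline and the significance level as "30-day survival was approximately 47%, assuming an alpha level of 0.5, two sided". The effect is given as "We expect the implementation of an IHVI Shock algorithm to increase 30-day survival by 15" per cent, with no target rate and no word on whether the gain is absolute or relative. It concludes: "Thus, 200 subjects in each group provide at least 80% power to detect a statistically significant increase in 30-day survival from 47" per cent.

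Number of Subjects repeats the size: "Our goal is to include approximately 200 patients before and 200 patients after initiation of Shock team".

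The Sample Size section, under Statistical Considerations and Data Analysis, says something else: "We are estimating 300-400 patients will be included in this analysis. This size is based on prior smaller studies". It mentions neither the power calculation nor 200 per group.

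The Abstract (Methods) and Method of Data Analysis both plan 95% confidence intervals for reported differences. Neither states a significance level.

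**The concern.** Three printed inputs need attention.

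- **Significance level.** A two-sided alpha of 0.5 would call half of all null comparisons significant. No other threshold is stated. The Study Type section itself warns of a raised type I error risk from historical controls, so the threshold should be printed correctly.
- **Effect size.** From a base of 47%, a gain of 15% means either 62% or 54.05%. The power with 200 per group differs greatly between the two.
- **Sample size.** One section derives 400 in total from power. Another estimates 300 to 400 from earlier small studies. The two agree only at the top of the range.

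At stake is whether a reader can reproduce the stated power, and whether a study that ends with fewer than 400 patients would still have it.

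**Working it through.** **Inputs**

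- Control 30-day survival p1 = 0.47 (Background and Significance).
- Gain of 15%: absolute p2 = 0.47 + 0.15 = 0.62; relative p2 = 0.47 × 1.15 = 0.5405.
- Alpha: 0.5 as printed, 0.05 as evidently meant; two-sided.
- Size: 200 per group, or 300 to 400 in total. For 300 I assume 150 + 150, because the article gives no split.
- No allowance for missing outcomes is stated, and none is used.

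**Formulas** (two proportions, normal approximation, equal groups, pooled variance under the null; d = p2 − p1, p̄ = (p1 + p2)/2)

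- Power = Φ[(d − z·s0)/s1], with s0 = √(2p̄(1 − p̄)/n) and s1 = √((p1(1 − p1) + p2(1 − p2))/n).
- n per group for 80% power = [z·√(2p̄(1 − p̄)) + 0.8416·√(p1(1 − p1) + p2(1 − p2))]² / d².

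**Step 1: the plan's own figure, with alpha 0.05 and an absolute gain.** Here p̄ = 0.545 and z = 1.960. With n = 200, s0 = 0.0498 and s1 = 0.0492. Power = Φ[(0.15 − 1.960 × 0.0498)/0.0492] = Φ(1.064) = 85.6%. The stated floor of 80% is met.

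**Step 2: the size needed for 80% on that reading.** n = (1.960 × 0.7042 + 0.8416 × 0.6962)² / 0.15² = 171.8, so 172 per group and 344 in total. With a continuity correction it is 185 per group, 370 in total.

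**Step 3: the relative reading, alpha 0.05.** Here d = 0.0705 and p̄ = 0.50525. With n = 200, s0 = 0.0500 and s1 = 0.0499. Power = Φ(−0.551) = 29.1%. Reaching 80% would take 789 per group.

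**Step 4: the printed alpha of 0.5** (z = 0.674). With the absolute gain, 200 per group give Φ(2.365) = 99.1%, and 51 per group would already reach 80%. With the relative gain, 200 per group give 77.0%.

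**Step 5: the lower end of the Sample Size range, alpha 0.05, absolute gain.** With n = 150, s0 = 0.0575 and s1 = 0.0568. Power = Φ[(0.15 − 1.960 × 0.0575)/0.0568] = Φ(0.656) = 74.4%. If the 300 were split 200 and 100, power would be about 69%.

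| Two-sided alpha | Gain | 150 per group | 200 per group | n per group for 80% |
|---|---|---|---|---|
| 0.05 | absolute, to 62% | 74.4% | 85.6% | 172 |
| 0.05 | relative, to 54.05% | 23.0% | 29.1% | 789 |
| 0.5 | absolute, to 62% | 97.5% | 99.1% | 51 |
| 0.5 | relative, to 54.05% | 70.8% | 77.0% | 231 |

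**The case against.** The strongest reply is that the power statement is sound once read sensibly. The article claims a floor, and 85.6% clears it. That stands. A reader might infer from the misprinted alpha that 200 per group does not deliver 80% power. The documents do not support that: the claim is true at 0.05 with an absolute gain, and also at the printed 0.5 with an absolute gain. Nor does the fact that about 50 per group would suffice at 0.5 contradict it, because the article never calls 200 the minimum.

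The intended values can also be inferred. The 95% intervals correspond to two-sided 0.05, no analysis rule uses 0.5, and at 0.05 only the absolute gain fits the claim. This shows what was meant. It does not make the printed figures right, and the reader has to calculate backwards to find the scale.

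On size, 400 lies within 300 to 400, both statements are approximate, and nothing says the study will stop at 300. That is fair, and the 74.4% also rests on an assumed equal split. But the range as written includes totals below 344, where the stated power is not met.

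A reader might also test the plan against the 57.9% survival reported for 2017. That would be power at an observed result, not a check of the planning assumption. The article also does not label that rate as 30-day survival.

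Finally, two reasons for a sample size can coexist. Nothing shows the appeal to earlier studies to be false, so it need not be deleted.

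**Conclusion.** The point holds for the printed inputs and for the lower end of the size range. It does not hold against the 200-per-group plan. The document's only significance level is wrong as printed, and the effect has no scale. At two-sided 0.05 with 200 per group, the choice of scale moves power from 85.6% (absolute) to 29.1% (relative). Under the evident reading (0.05, 47% to 62%) the claim of at least 80% is correct. The Sample Size section's range reaches below the 344 patients needed for it, and 300 in total gives 74.4%.

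These figures assume equal groups, a normal approximation with pooled null variance, and complete outcome data. With a continuity correction the requirement rises to 370 in total. An unequal split of 300 would lower the power further.

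**What to change.** In Background and Significance, restate the assumptions as: two-sided alpha 0.05; 30-day survival rising from 47% to 62% (15 percentage points); 200 per group gives about 86% power.

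In Sample Size, either give the same 200 + 200 as Number of Subjects, or keep the range and say that 300 in total gives about 74% power with equal groups. The reference to earlier small studies may stay beside the power calculation.

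The cost is wording only. The target of 200 per group does not change. If the range is kept, its lower end carries a less favourable power figure.

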### Specific Aims

The specific aims of this study are as follows: (1) to collect retrospective clinical outcomes related to acute decompensated heart failure cardiogenic shock, acute myocardial infarction cardiogenic shock and compare current versus historical survival rates; (2) to collect Inova Heart and Vascular Institute (IHVI) site specific outcomes before and after initiation of the Cardiogenic Shock team on January 1, 2017; (3) outcomes related to implementation of mechanical circulatory support versus no circulatory intervention and type of intervention (ECMO versus intracorporeal axial-flow [Impella]); and (4) to assess survival at 3 time points.

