**Objective:**

The objectives of this study are (1) to collect retrospective clinical outcomes for acute decompensated heart failure cardiogenic shock and acute myocardial infarction cardiogenic shock, and compare current versus historical survival rates and clinical outcomes; (2) to evaluate Inova Heart and Vascular Institute site specific outcomes before and after initiation of the Cardiogenic Shock team on January 1, 2017; (3) to compare outcomes related to early implementation of mechanical circulatory support and hemodynamic-guided management versus historical controls; (4) to assess survival to discharge rate in patients receiving intervention from the designated shock team and (5) create a clinical archive of Cardiogenic Shock patient characteristics for future analysis and the support of translational research studies.

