#### Secondary Outcomes

Analysis of mortality by subgroup (age, sex, initial etiology, time to presentation, time to treatment, use of mechanical circulatory support, Incidence of major adverse cardiac and cerebrovascular events, and preservation of left ventricular function.

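### The contrast of mechanical circulatory support with no support has no time zero or start window, so deaths before device placement count against no support

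*Protocol article*

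**What the plan says.** Specific Aims, item 3, names the two groups: "outcomes related to implementation of mechanical circulatory support versus no circulatory intervention". It then adds type of support, ECMO against Impella. Secondary Outcomes repeats "use of mechanical circulatory support" as a mortality subgroup in the same list as age and sex. The mortality endpoint in Primary Outcomes is death from any cause by discharge.

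Neither place says when the clock starts, by when support must have begun, or how to class a patient who dies before placement. On timing of placement, Background and Significance says of the interventional cardiology group: "This group assists with mechanical circulatory assist device insertion and management both on hospital admission and throughout hospitalization". Method of Data Analysis gives only summaries by group, and differences with standard errors and 95% confidence intervals.

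Two further passages bear on the exposure:

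- The abstract's third objective is worded differently: "to compare outcomes related to early implementation of mechanical circulatory support and hemodynamic-guided management versus historical controls". It has the word early and another comparator.
- The article's only list of what MCS covers stands in the Background, in a sentence on team goals. It follows "maximization of survival through the utilization of mechanical circulatory support" and ends with "central ECMO; temporary vascular assist device; permanent vascular assist device; or transplant".

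**The concern.** A device can be recorded only in a patient who lived long enough to receive one. If patients are grouped by whether they ever had MCS and compared on discharge survival, every death before placement falls in the no-support group, including deaths of patients for whom a device was intended. The time from shock to device is guaranteed survival for the MCS group. This is immortal-time bias, and per-group summaries with a difference do not remove it.

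Two records show the mechanism. A patient who dies a few hours after onset, before a device can be placed, is entered as no support, dead. A patient with the same prognosis at onset who lives until placement is entered as MCS. How long each lived decides the group.

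The study's hypothesis includes rapid initiation of MCS, so an MCS advantage created by the grouping would readily be taken as support for it.

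**Working it through.** The article gives no figure for this contrast. The one input it supplies is 2017 survival in Results, 81/140 = 57.9%. (The abstract prints 58/110 beside the same percentage, but 58/110 = 52.7%, so the Results counts are used.)

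**Step 1. Closed form with no MCS effect.** Let S be survival, m the share of patients who would get a device if they lived long enough, and q the share of deaths among those patients that occur before placement. S = 0.5786. Assumed, not in the article: m = 50% or 70%, q = 5% to 30%.

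- Survival with MCS = S / [1 − (1 − S)q]
- Survival without = (1 − m)S / [(1 − m) + m(1 − S)q]

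For m = 0.5, q = 0.10: 0.5786/(1 − 0.0421) = 60.4%, against 0.2893/(0.5 + 0.0211) = 55.5%. The spurious difference is 4.9 points.

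| m | q | MCS % | No MCS % | Difference (points) |
|---|---|---|---|---|
| 50% | 5% | 59.1 | 56.7 | +2.4 |
| 50% | 10% | 60.4 | 55.5 | +4.9 |
| 50% | 20% | 63.2 | 53.4 | +9.8 |
| 50% | 30% | 66.2 | 51.4 | +14.9 |
| 70% | 5% | 59.1 | 55.1 | +4.0 |
| 70% | 10% | 60.4 | 52.7 | +7.7 |
| 70% | 20% | 63.2 | 48.3 | +14.8 |
| 70% | 30% | 66.2 | 44.7 | +21.6 |

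Differences are taken from unrounded values.

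**Step 2. Simulation with explicit times, still no MCS effect.** There were 2,000,000 patients per scenario. Assumed: m = 50% or 70%, exponential time to device with mean 10 or 24 h, and lognormal time to death with median 48 or 96 h and log-SD 1.2. Deaths before placement come to 4% to 24% of deaths among the device-intended. The ever/never difference is about 2 to 17 points in favour of MCS. The closed form agrees at both ends: m = 0.5, q = 0.04 gives 58.9 − 56.9 ≈ 2 points, and m = 0.7, q = 0.236 gives 64.3 − 47.0 ≈ 17 points.

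**Step 3. Landmark.** In the same scenarios, patients alive at 12 h were grouped by support started by 12 h. The difference is zero to within 0.3 points. The 12 h is for illustration only.

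**Step 4. Add selection of sicker patients.** Assume candidates have a death risk 10 points higher than non-candidates, with overall survival still 57.9%. Candidate survival is S − (1 − m) × 0.10.

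- m = 0.5, q = 0.10: candidates 52.9%, others 62.9%. MCS 0.5286/0.9529 = 55.5%; no MCS 0.3143/0.5236 = 60.0%. Difference −4.6 points.
- m = 0.7, q = 0.20: candidates 54.9%, others 64.9%. MCS 0.5486/0.9097 = 60.3%; no MCS 0.1946/0.3632 = 53.6%. Difference +6.7 points.

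Across the Step 2 scenarios with this gap, the ever/never difference runs from about −8 to +9.5 points and is against MCS in 5 of 8. The 12 h landmark then gives about −4 to −8 points: it removes the immortal time and leaves the confounding.

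**The case against.** The strongest reply is that the article does not write the faulty rule. Aim 3 is one clause and the subgroup is one phrase. Exposure windows and time-dependent coding are often left to a full protocol or analysis plan, and neither is shown. Part of this stands: no sentence says that support begun at any time counts. That is a reading of the missing window together with the Background remark on insertion throughout the stay. The point survives because the aim itself names the two groups, the only analysis stated is a difference between groups, and following those words produces the bias.

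A reader might go further and infer that the plan counts transplant and permanent devices as MCS exposure. The documents do not support that. The list is a Background statement of team goals. Aim 3 itself names ECMO and Impella, and Exclusion Criteria separates temporary from durable support. The list is a source of ambiguity and does not define the exposure.

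A reader might also infer that MCS will look beneficial even if it does nothing. That holds for this mechanism alone. Step 4 shows that a modest excess risk in device candidates can cancel or reverse it.

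The early-support objective in the abstract is a different contrast, against historical controls. Aim 3 cannot be faulted for failing to measure it, although the two wordings do need reconciling. The subgroup phrase might also mean before/after mortality within MCS strata.

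The rest of the article does not answer the point. Study Type admits limits of historical controls only. Exclusion Criteria removes patients unsuited to support, but not candidates who die before placement. Results and Discussion relate survival to how soon MCS began, with arrival as the Discussion's clock. That compares earlier with later support and does not repair a comparison with none.

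**Conclusion.** The concern holds for Aim 3 and for the MCS subgroup. As worded, the contrast carries immortal-time bias in favour of MCS, illustratively about 2 to 17 points of discharge survival with no true effect. Only 81/140 comes from the article; the share of patients intended for a device and the device and death times are assumptions. The range shows the mechanism and does not estimate the error in this registry. Because confounding by indication may act in the opposite direction, the net bias is of unknown sign, and the printed difference could not be read as evidence for or against MCS.

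This is a secondary comparison. The before/after primary comparison and its sample size do not depend on it. The change is worth making, but the study's main result does not hang on it.

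**What to change.** In Specific Aims and Secondary Outcomes:

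1. Set a time zero for the MCS contrast, for example documented shock onset or team activation.
2. Compare by a landmark at a fixed analysis time after it, among patients alive then and grouped by temporary support already started. Alternatively, treat MCS as a time-dependent exposure.
3. Report deaths before the landmark separately.
4. Describe the remaining contrast as confounded by indication unless it is adjusted for baseline severity.
5. State that a later durable device or transplant is a disposition and not MCS exposure, so that the Background list is not used as a coding rule.
6. Reconcile the abstract's third objective (early MCS against historical controls) with Aim 3 (MCS against none), or state both as separate comparisons.

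The cost is wording and one variable derived from chart times. Results already reports time to MCS, so device timing is being abstracted. The downside is that patients who die before the landmark leave this comparison. With the illustrative 12 h, that is 0.421 × 12.4% ≈ 5% of patients if median time to death is 48 h, and 0.421 × 4.2% ≈ 2% if it is 96 h. A time-dependent exposure avoids this loss.
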